## Abstract

**Background:**

Depressive disorders are the third leading cause of consultation in primary care, mainly in patients with chronic physical illnesses. Studies have shown the effectiveness of group psychoeducation in reducing symptoms in depressive individuals. Our primary aim is to evaluate the effectiveness of an intervention based on a psychoeducational program, carried out by primary care nurses, to improve the remission/response rate of depression in patients with chronic physical illness. Secondarily, to assess the cost-effectiveness of the intervention, its impact on improving control of the physical pathology and quality of life, and intervention feasibility.

**Methods/design:**

A multicenter, randomized, clinical trial, with two groups and one-year follow-up evaluation. Economic evaluation study.

**Subjects:**

We will assess 504 patients (252 in each group) aged > 50 years assigned to 25 primary healthcare centers (PHC) from Catalonia (urban, semi-urban, and rural). Participants suffer from major depression (Beck depression inventory: BDI-II 13–28) and at least one of the following: type 2 diabetes mellitus, chronic obstructive pulmonary disease, asthma, and/or ischemic cardiopathy. Patients with moderate/severe suicide risk or severe mental disorders are excluded. Participants will be distributed randomly into the intervention group (IG) and control (CG).

**Intervention:**

The IG will participate in the psychoeducational intervention: 12 sessions of 90 min, once a week led by two Primary Care (PC) nurses. The sessions will consist of health education regarding chronic physical illness and depressive symptoms.

**Main measurements:**

Clinical remission of depression and/or response to intervention (BDI-II).

**Secondary measurements:**

Improvement in control of chronic diseases (blood test and physical parameters), drug compliance (Morinsky-Green test and number of containers returned), quality of life (EQ-5D), medical service utilization (appointments and hospital admissions due to complications), and feasibility of the intervention (satisfaction and compliance). Evaluations will be blinded, and conducted at baseline, post-intervention, and 12 months follow-up.

**Discussion:**

Results could be informative for efforts to prevent depression in patients with a chronic physical illness.

**Trial registration:**

NCT03243799 (registration date August 9, 2017)

## Background

Depression is considered a major public health issue in industrialized societies [1], and has been associated with greater morbidity and mortality, and increased healthcare utilization and costs [2–4]. In primary care, depression is one of the most frequent causes of consultation [5] and is particularly common in patients with physical illnesses. The prevalence of depression worldwide is 4.4%, in Spain it represents 5.2% [6] reaching up to 30% in populations with chronic physical conditions when taking into account symptoms and disorders [2]. For instance, in diabetic patients the risk of depression is twice that of the general population [2]. According to the World Health Organization (WHO) by 2030 it will be the principal cause of disability in the world [7].

The concomitance of physical illness and depression not only decreases the patient’s response to anti-depressive treatment but also worsens control of their organic pathologies, results in unhealthy habits (diet and exercise), and leads to lower treatment compliance [8]. As a consequence, the economic burden of healthcare is greater in such individuals with depression than those without [7]. For instance, patients with depression and chronic obstructive pulmonary disease (COPD) can present exacerbations of common respiratory symptoms which require a greater number of visits to the emergency room and hospitalization [9]. It is thus becoming increasingly necessary to design strategies aimed at detecting and treating depression in patients with associated physical comorbidity in order to reduce depressive symptoms and disorders, and improve general health.

A number of studies has shown that preventive interventions, particularly stepped-care ones, can lead to a reduction of up to 25% in the rate of depression in diseases such as diabetes [10]. Most of the research, however, has been focused on reducing depressive symptoms and disorders, and there is less directed at obtaining health benefits regarding the parameters of the associated medical illness [11, 12]. According to the literature, there are greater benefits to be had from intervening rather than not [10,11,]. Nevertheless, there is some controversy over whether specific and specialized interventions are better than more general ones such as health education regarding the associated chronic pathologies [13, 14]. As an example, the DIAMOS study reported that behavioral techniques led to both a decrease in depressive symptoms and a reduction in blood glucose levels [15].

With regard to psychoeducation, it has been demonstrated that it is an effective therapy in the treatment of depression in adults [16, 17] as it decreases depressive symptoms and risk of relapse/recurrence, and improves treatment compliance [17–19]. Adherence to psychoeducation interventions is high, according to some authors, with a reported attendance of 73–87% in all the group sessions [18, 20]. Moreover, such therapy could be carried out in primary care by community nurses with previous training [18, 20].

We present a study protocol of a randomized controlled trial aimed at evaluating the effectiveness of a psychoeducation group intervention carried out by primary care nurses in patients with depression and chronic physical illness (diabetes, COPD, asthma and/or ischemic cardiopathy). The main objective is to evaluate whether such an intervention improves the rate of remission and response of depression in these patients. Secondary ones include assessing the cost-effectiveness and feasibility of the intervention, its efficacy in improving control of the physical pathology, and its impact on health-related quality of life (HRQoL).

The primary hypothesis is that in patients with chronic physical disease pyschoeducation group therapy provided by primary care nurses can achieve a greater rate of remission and response of depression than habitual clinical practice.

## Methods/design

### Study design

A randomized, multi-center, clinical trial composed of two groups with blinded response variables and a one-year follow-up. A cost-effectiveness study will also be performed. When each primary healthcare center (PHC) has a sample of 24 patients these are randomly allocated to either an intervention group (IG) or a control (CG). Data will be collected at baseline, and at 3 and 12 months post-intervention.

### Sample

The participants are patients aged > 50 years assigned to PHC from different locations: Barcelona city (1,200,066), the central area of Catalonia (192,000), and the southern area (132,000). Such a territorial representation provides patients from urban, semi-urban, and rural areas.

Inclusion criteria are: 1) the presence of at least one of the following physical diseases: diabetes mellitus type 2, COPD, asthma, and ischemic cardiopathy; 2) a score > 12 on the Beck Depression Inventory score (BDI-II) [21, 22] Spanish version adapted by Sanz et al. [23–25], and confirmation of major depression according to DSM-IV criteria with the Mini International Neuropsychiatric Interview (MINI); 3) adherence to a one-year follow-up with the same PHC team; 4) signed informed consent.

Exclusion criteria are: 1) diagnosis of dementia or moderate/elevated cognitive decline (5 or more errors on the Pfeiffer scale); 2) major depressive disorder with psychotic symptoms or other serious psychiatric comorbidities; 3) elevated/moderate risk of suicide (a score of ≥6 on the MINI scale); 4) drug of abuse dependence disorders (including alcohol); 5) physical illness at an advanced stage; 6) inability to attend the PHC; 7) under psychological therapy from the Community Mental Health Team; 8) inability to understand Spanish/Catalan.

Patients receiving anti-depressive/anxiolytic treatment are not excluded. Their data are collected and considered as covariables.

### Sample size

A power analysis will be conducted to determine the appropriate sample size. A previous study of psychoeducation programs [18] reported a remission rate at 9 months follow-up of 40% in the IG and 26% in the CG. Assuming a 5 and 20% alpha and beta risk, respectively, 189 patients are required for each group. Due to a number of reasons, an approximately 25% dropout rate is expected, consequently, 252 participants per group need to be recruited (total *n* = 504). In addition, 25 PHC are required each with a mean of 20 patients (IG *n* = 10, CG *n* = 10).

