### Intervention

#### Description of the psychoeducation group intervention

In order to homogenize the interventions, the research group has developed a protocol of 12 weekly sessions lasting 90 min led by two primary care nurses. Each group is made up of 8–12 participants [26]. The sessions will be held on PHC premises which have the necessary space and equipment.

The objectives of the 12 sessions are depicted in Table 1. The program provides: 1) health education about chronic pathology and depressive symptoms; 2) information on the relationship between depressive symptoms and chronic pathology; 3) health education regarding: diet, physical exercise, sleep, pleasant activities, social skills, pharmacological treatment, and adherence to treatment; 4) breathing techniques; 5) problem solving, behavioral activation, and cognitive-behavioral perspective on depression; and 6) self-esteem and assertiveness [26].

**Table 1 Tab1:** Content of the psychoeducational group program

lSessions	Objectives
1	• First contact with the group • Identification of depressive symptoms • Information on chronic pathology versus chronicity • Information on the relationship between depressive symptoms and chronic pathology • Breathing techniques
2	• Behavioural Activation I: Concern and problems.
3	• Behavioural Activation II: Concern and problems.
4	• How to take care to advance I ➢ Healthy diet ➢ Motivation for change (resources and difficulties)
5	• How to take care to advance II ➢ Physical exercise ➢ Pleasant activities, social skills
6	• How to take care to advance III ➢ Sleep ➢ Therapeutic compliance
7	• Problem solving I
8	• Problem solving II
9	• Self-esteem and assertiveness
10	• Cognitive-behavioural perspective I
11	• Cognitive-behavioural perspective II
12	• Group farewell • Final evaluation

To enhance the active role of the patient, each session is accompanied with homework. The participants are free to continue under pharmacological treatment.

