### Recruitment process

The recruitment process for the trial began in September 2017. All eligible PHC located in Barcelona city, the central area of Catalonia (Bagés, Berguedá, and Solsonés) and the southern area (Baix Llobregat Nord) have been contacted and encouraged to participate in the study. The PHC who express interest receive a team presentation, explanatory dossiers, and informed consent papers. Those who wish to take part are required to consecutively recruit 16–24 patients who, after meeting inclusion criteria and signing the informed consent, will be randomized into two equally sized groups (IG and CG).

Different groups of healthcare workers will be involved in the field work:Recruiters: the patient’s assigned doctor and/or nurse.Nurses leading the psycho-educational groups, two per PHC.Evaluators blinded to the groups who carry out interviews at baseline, and at 3 months, and 12 months post-intervention.An external researcher in charge of patient randomization which is performed once all the necessary number of patients have signed the consent forms. The data gathering phases are explained in the work plan section.

All outcome variables will be assessed three times: prior to study commencement (baseline), after 3 months, and at 12 months after inclusion in the individual data collection sessions. Information about data collection and intervention programme timeline are detailed in the Table 2.

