### Statistical analysis

The analysis is performed on an intention-to-treat basis. All the patients who have signed the informed consent and attended the initial interview are included. Missing data from the BDI-II evaluation during follow-up will be substituted by the last registered value (Last Observation Carried Forward strategy). At the beginning of the study descriptive statistics will be performed to evaluate the homogeneity between the two groups (IG and CG) with respect to demographic, clinical, and service utilization variables. In order to measure the main objective (rate of remission and response) logistic regression is employed in which the dependent variable is dichotomous (rate of remission and response). The patient’s group is the independent variable. Raw and adjusted odds ratio (OR) are calculated according to age, sex, pharmacologic treatment, and comorbidity. Repeated measure ANOVA analysis will be performed to determine the evolution of the dependent variables during follow-up. For the secondary resulting variables, control of the physical pathologies will be measured by logistic regression in which the dependent variable is dichotomous (control yes/no). The models will be adjusted in the same way as the principal one. Variable differences in the BDI-II rating and other scores with respect to baseline will be calculated. Student’s t test will be employed for the comparison between the groups’ variables and standardized effect size (SES; Kazis et al.1989) [44].

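### Intervention patients are treated in shared nurse-led groups, but the sample size and the primary logistic model treat all patients as independent, so 5% type I error and 80% power are not assured

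*Protocol article*

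**What the plan says.** **Sample size (Protocol article).** The planning rates come from an earlier psychoeducation study that "reported a remission rate at 9 months follow-up of 40% in the IG and 26% in the CG". From these, "Assuming a 5 and 20% alpha and beta risk, respectively, 189 patients are required for each group". The only inflation is for dropout: "an approximately 25% dropout rate is expected, consequently, 252 participants per group need to be recruited". The section adds that "25 PHC are required each with a mean of 20 patients", split 10 and 10 between the arms.

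**Intervention and control.** Under the description of the intervention, "Each group is made up of 8–12 participants", meeting for 12 weekly sessions led by two nurses. Recruitment process gives two group-leading nurses per PHC. Controls see their own doctor or nurse individually, as needed.

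**Allocation.** Patients are randomised individually and equally between the arms, PHC by PHC.

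**Statistical analysis.** The main objective is tested by logistic regression: "The patient’s group is the independent variable", with raw odds ratios and odds ratios adjusted for age, sex, pharmacological treatment and comorbidity. The models for control of the physical illness are adjusted in the same way. Neither the therapy group nor the PHC is listed.

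**The concern.** Ten intervention patients per PHC, groups of 8 to 12 and two leaders per PHC together imply about one therapy group per PHC, so about 25 groups. The article does not say this outright; it is an inference. Members of a group share sessions, leaders and group dynamics, so their outcomes may be correlated. Controls have no such shared unit. This is an individually randomised trial with clustering in one arm.

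A model that ignores the correlation understates the variance of the intervention-arm proportion. Its p-values are then too small and its confidence intervals too narrow. A test that does respect the groups has less power than the independent-patient formula promises. At stake is whether a primary result near the 5% boundary can be taken at face value. Recruiting more patients under the same model would not cure the type I error.

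**Working it through.** **Inputs from the article.** Remission 40% v 26% (difference 0.14, mean 0.33), alpha 5%, power 80%, 189 evaluable and 252 recruited per arm, 25 PHC, 10 intervention patients per PHC, groups of 8 to 12. Sidedness is not stated; two-sided fits.

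**Inputs assumed.** Therapy-group ICC 0.01 to 0.10 (no ICC is given), and clustering in the intervention arm only.

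**1. The plan's figure.**
- Uncorrected: n = [1.96·√(2·0.33·0.67) + 0.842·√(0.40·0.60 + 0.26·0.74)]² / 0.14² = 175.9.
- Continuity-corrected: n/4·[1 + √(1 + 4/(n·0.14))]² = 189.9, against the stated 189.
- Dropout: 189/0.75 = 252 exactly.

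The stated numbers therefore leave no room for a design effect. Logistic regression applies no continuity correction, so the fair starting point is the uncorrected power at 189 per arm with independent patients, which is 82.8%.

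**2. Group size.** 189/25 = 7.56 evaluable per group. Groups of 10 are shown as well; with 189 evaluable that would mean about 19 groups.

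**3. Formulas.** The design effect in the intervention arm is DE = 1 + (m − 1)·ICC; in the control arm it is 1.
- Type I error of the planned test = 2·[1 − Φ(1.96/√((1 + DE)/2))].
- Power of a test that respects the groups = Φ[(0.14 − 1.96·SE0)/SE1], with SE0 = √(0.33·0.67·(1 + DE)/189) and SE1 = √((0.24·DE + 0.1924)/189).

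**4. Example, m = 7.56 and ICC 0.05.** DE = 1 + 6.56·0.05 = 1.328. Type I error = 2·[1 − Φ(1.96/√1.164)] = 6.9%. SE0 = 0.05219 and SE1 = 0.05200, so power = Φ[(0.14 − 0.1023)/0.0520] = 76.6%.

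**5. Range.**

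| ICC | Type I, m = 7.56 | Power, m = 7.56 | Type I, m = 10 | Power, m = 10 |
|---|---|---|---|---|
| 0 | 5.0% | 82.8% | 5.0% | 82.8% |
| 0.01 | 5.4% | 81.5% | 5.5% | 81.0% |
| 0.02 | 5.8% | 80.2% | 6.0% | 79.3% |
| 0.05 | 6.9% | 76.6% | 7.7% | 74.4% |
| 0.10 | 8.9% | 70.9% | 10.4% | 67.0% |

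Valid power falls below 80% above an ICC of about 0.022 (m = 7.56) or 0.016 (m = 10).

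**6. Simulation of the planned unadjusted test** (25 PHC, 8 or 10 patients per arm per PHC, 26% remission in both arms). Type I error was 5.8–6.0% at group ICC 0.02, 7.0–7.4% at 0.05 and 9.3–10.7% at 0.10, in line with the formula. With no group effect but a PHC effect shared by both arms (ICC 0.05), it was 4.4–4.5%. With group and PHC ICC both 0.05, it was 6.5–7.1%.

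**The case against.** **Power is not shown to be missed.** A reader might infer that 80% power will not be delivered. The documents do not support that. They give no ICC, and the continuity correction leaves a small reserve, so 80% survives up to an ICC of about 0.016 to 0.022. "Not assured" is as far as the evidence goes. This objection stands.

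**The missing PHC term is not the cause.** A reader might also blame the omission of PHC, the unit within which patients are randomised, for the excess type I error. It works the other way: a PHC effect shared by both arms is balanced by randomisation within PHC, and ignoring it makes the test slightly conservative. That can partly offset the group effect. Applying a design effect to both arms (275 evaluable per arm at ICC 0.05 and m = 10) would likewise overstate the loss.

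**Last observation carried forward may enlarge the sample.** The plan could bring all 252 per arm into the analysis. With 10 per group and ICC 0.05, valid power is then about 86% if 40% v 26% still holds. If the 25% who drop out carry forward non-remission (30% v 19.5%), it is about 69%, and 78% even with no clustering. So carrying forward is no dependable reserve, and the tabulated figures describe 378 evaluable patients, not 504.

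**The analysis plan may cover it.** Variance structure is often left to that document, which is not shown. This has limited weight: the article itself names the model, lists its covariates and fixes the sample size, all on the basis of independence.

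**Conclusion.** The point holds in a limited form. The stated sample size and the stated primary model both assume independence that the group-delivered intervention does not provide. Confidence is high on this structure and lower on the size of the effect, which rests on an assumed ICC, on clustering in the intervention arm only and on the inferred one group per PHC.

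For any positive therapy-group ICC that a shared PHC effect does not offset, the planned test exceeds 5%. Over ICC 0.01 to 0.10 with about 7.6 evaluable per group, type I error is 5.4% to 8.9% and valid power 81.5% to 70.9%. With 10 per group, the figures are 5.5% to 10.4% and 81.0% to 67.0%.

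**What to change.** **Statistical analysis.** Account for the therapy group in the primary and secondary models. Either include a random intervention effect by PHC together with PHC as randomisation stratum, or use PHC-cluster-robust standard errors with a small-sample correction for about 25 clusters. A PHC intercept alone does not repair the problem, because the inflation comes from the treatment groups in one arm.

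**Sample size.** State an assumed therapy-group ICC and its basis. In place of the single 80%, give the power for 189 evaluable per arm as a range over the ICC, for example 81.5% to 70.9% for ICC 0.01 to 0.10 at about 7.6 per group. Do not attach these figures to 504 patients.

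**Cost.** A few sentences, slightly wider confidence intervals and a less favourable stated power. No extra patients are needed for a valid test, but the change does not restore 80% power. At ICC 0.05 that would take about 206 evaluable (275 recruited) per arm with 7.56 per group, or 217 (290) with 10 per group. The sponsor should make that choice openly.

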### Intervention

#### Description of the psychoeducation group intervention

In order to homogenize the interventions, the research group has developed a protocol of 12 weekly sessions lasting 90 min led by two primary care nurses. Each group is made up of 8–12 participants [26]. The sessions will be held on PHC premises which have the necessary space and equipment.

The objectives of the 12 sessions are depicted in Table 1. The program provides: 1) health education about chronic pathology and depressive symptoms; 2) information on the relationship between depressive symptoms and chronic pathology; 3) health education regarding: diet, physical exercise, sleep, pleasant activities, social skills, pharmacological treatment, and adherence to treatment; 4) breathing techniques; 5) problem solving, behavioral activation, and cognitive-behavioral perspective on depression; and 6) self-esteem and assertiveness [26].

**Table 1 Tab1:** Content of the psychoeducational group program

lSessions	Objectives
1	• First contact with the group • Identification of depressive symptoms • Information on chronic pathology versus chronicity • Information on the relationship between depressive symptoms and chronic pathology • Breathing techniques
2	• Behavioural Activation I: Concern and problems.
3	• Behavioural Activation II: Concern and problems.
4	• How to take care to advance I ➢ Healthy diet ➢ Motivation for change (resources and difficulties)
5	• How to take care to advance II ➢ Physical exercise ➢ Pleasant activities, social skills
6	• How to take care to advance III ➢ Sleep ➢ Therapeutic compliance
7	• Problem solving I
8	• Problem solving II
9	• Self-esteem and assertiveness
10	• Cognitive-behavioural perspective I
11	• Cognitive-behavioural perspective II
12	• Group farewell • Final evaluation

To enhance the active role of the patient, each session is accompanied with homework. The participants are free to continue under pharmacological treatment.

#### Description of the control group

Members of the CG receive their usual treatment, that is to say, they can consult their family doctor/nurse as needed with no set pattern. The appointments last from 10 to 20 min and for both groups the healthcare professionals use their own criteria (usual clinical practice) regarding the chronic pathology and depressive symptoms.

The nurses receive prior training based on the intervention protocol [26] including the content of the 12 sessions. It consists of 20 h (10 theory and 10 practice) and is given by psychologists and nurses specialized in mental health.

